#### Analyses of the key secondary outcomes

The secondary outcomes will be analyzed as described for the primary outcome. The third secondary outcome of all-cause mortality and stroke will use the Kaplan–Meier estimator to visualize survival times. The comparison is based on the Cox proportional-hazard model with two-sided 95% CIs. All secondary outcome analyses will be considered exploratory.

#### Sensitivity analyses

Sensitivity analyses based on PP allocation will be used to test the robustness of the primary analyses. The statistical analyses are equivalent to those described above. Moreover, a complete-case analysis will be performed.

#### Subgroup analyses

Subgroup analyses will investigate the interaction of outcomes and key stroke risk factors. Predefined analyses are as follows:I.Prior stroke, including TIAII.Prior AFIII.Recurrent AFIV.Pre-operative CHA_2_DS_2_-VASc scoreV.Preoperative and postoperative OACVI.Preoperative and postoperative antiplatelet therapy

The interaction terms will be added to the Cox models described in the primary and secondary outcome analyses above. A significant subgroup effect will be considered if the *p*-value ≤ 0.05. Each interaction term’s HR and 95% CI will be presented in a forest plot.

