## Statistical principles

### Confidence intervals and *P* values

A significance level of 5% and a confidence interval of 95% will be applied. No multiplicity adjustment is planned; consequently, findings in secondary outcomes are considered exploratory. Only two-sided significance tests will be used.

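### The subgroup forest plot will show ratios of hazard ratios, not the effect of LAA closure in each subgroup, and subgroup effects on the primary outcome are declared at unadjusted p ≤ 0.05 with no exploratory label

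*SAP article*

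**What the plan says.** The Subgroup analyses section of the SAP article names six items: prior stroke or TIA, prior AF, recurrent AF, preoperative CHA2DS2-VASc score, and two combined items, "Preoperative and postoperative OACVI.Preoperative and postoperative antiplatelet therapy". On the models it says: "The interaction terms will be added to the Cox models described in the primary and secondary outcome analyses above". On the decision it says: "A significant subgroup effect will be considered if the" p-value is no greater than 0.05. On the display it says that each interaction term's "HR and 95% CI will be presented in a forest plot".

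Two other places bear on how these results are to be read. Confidence intervals and P values states: "No multiplicity adjustment is planned; consequently, findings in secondary outcomes are considered exploratory". Analyses of the key secondary outcomes adds: "All secondary outcome analyses will be considered exploratory". The Subgroup analyses section itself has no sentence on exploratory status.

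**The concern.** There are two separate problems, and the display is the more concrete one.

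**Display.** A subgroup forest plot is read as showing how well treatment works in each group. The exponentiated coefficient of an interaction term in a Cox model does not show that. It compares the treatment effect in one group with the effect in another, and a value of 1 means that the effects are equal, whether closure helps, harms or does nothing in both. The article's Background and rationale gives patients without AF and at low stroke risk as the open question. As written, the plot would leave out the estimate for those patients and put in its place a number that looks like it.

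**Declaration rule.** Each modifier is tested on the primary outcome at the same 0.05 threshold as the main hypothesis, with no adjustment and no exploratory status. A chance interaction by AF or by CHA2DS2-VASc score could be reported as an established difference in effect, in the part of the trial that readers will look to when deciding whom the result applies to.

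**Working it through.** **1. What the interaction HR is.** For a binary modifier M (for example prior AF), the model is

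log hazard = baseline + b1·closure + b2·M + b3·(closure × M) + stratification factors.

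- Treatment HR when M = 0: exp(b1)
- Treatment HR when M = 1: exp(b1 + b3)
- HR of the interaction term: exp(b3) = (HR when M = 1) / (HR when M = 0)

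As an illustration, the planned rates of 1.2% and 3.0% per year (Sample size) give a ratio of 1.2/3.0 = 0.4. If closure has HR 0.4 in both groups, the interaction HR is 0.4/0.4 = 1. If closure has no effect in either group, it is 1/1 = 1. The planned plot cannot tell these two results apart. The same fitted model gives exp(b1) and exp(b1 + b3) with their confidence intervals, so no further modelling is needed to show them.

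**2. How many tests lack a label.**

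| Input | Value | Source |
|---|---|---|
| Modifiers | 6, or 8 if pre- and postoperative OAC and antiplatelet therapy are tested separately | Subgroup analyses |
| Outcomes | 1 primary + 3 secondary = 4 | Outcome definitions; Subgroup analyses |
| Threshold per test | 0.05 | Subgroup analyses |

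Counting one test per modifier, the total is 6 × 4 = 24 to 8 × 4 = 32 tests. Of these, 6 × 3 = 18 to 8 × 3 = 24 concern secondary outcomes and are labelled exploratory. The remaining 6 to 8, on the primary outcome, are not.

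**3. Chance of a false declaration on the primary outcome.** The article gives no error rate for these tests, so there is no figure to reproduce. With k independent tests and no true interaction, the chance is 1 − 0.95^k:

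- k = 6: 1 − 0.95^6 = 1 − 0.735 = 26.5%
- k = 8: 1 − 0.95^8 = 1 − 0.663 = 33.7%
- Expected number of false declarations: 6 × 0.05 = 0.3 to 8 × 0.05 = 0.4

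Independence is an assumption. Prior stroke is part of the CHA2DS2-VASc score, AF and OAC use go together, and pre- and postoperative use of the same therapy overlap. Such dependence lowers the familywise figure, with 5% as the limit if all the tests were in effect one test. The documents do not allow the true value to be fixed within that range.

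**4. How much an interaction test can show here.** The plan expects 16 and 39 primary events (Sample size). This reproduces: 1302/2 = 651 per arm, 651 × 0.024 = 15.6 and 651 × 0.060 = 39.1, about 55 in all. Assume a binary modifier that splits these events evenly, so that each level has 8 and 19.5:

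- Variance of the log HR in one level: 1/8 + 1/19.5 = 0.176
- Standard error of the log ratio of HRs: √(2 × 0.176) = 0.59
- The 95% CI reaches a factor of exp(1.96 × 0.594) = 3.2 in each direction
- Ratio of HRs needed for 80% power: exp((1.96 + 0.842) × 0.594) = 5.3

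Uneven splits are less precise. A p-value above 0.05 therefore says little about consistency of effect, and a single p-value below it among six to eight tests is weak evidence of a difference.

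**The case against.** **The labelling complaint can be overstated.** A reader might infer that the subgroup tests on all four outcomes lack an exploratory label, and so compute an error rate over all 24 to 32 tests. The documents do not support that. Two sections label the secondary outcomes exploratory, and those account for 18 to 24 of the tests. Only the primary-outcome tests are left uncovered. This objection stands, and the figures above are limited accordingly.

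**Unadjusted interaction tests on a short prespecified list are ordinary practice.** The plan uses formal interaction tests instead of comparing within-subgroup p-values, and says openly that nothing is adjusted. The superiority rule under Analyses of the primary outcome rests only on the HR for randomization, and the primary objective is the overall effect whatever the AF status or CHA2DS2-VASc score. All of this is right. It follows that the lack of adjustment is not itself an error, and that the plan does not make any subgroup result confirmatory. What remains is that the article states a rule for declaring significance and gives these tests no status.

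**The forest-plot sentence may be loose shorthand** for HRs derived from the interaction models, and figure layout is often left to a fuller document. That may be what is meant. But the sentence does name a plotted quantity, it is not the usual one, and no other sentence promises the subgroup-level HRs. A stated purpose of the plan is to make the analyses transparent, so the quantity should be named correctly.

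**Conclusion.** The point holds in two limited parts.

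- **Forest plot.** As written, it shows ratios of hazard ratios and omits the effect of closure within each subgroup. This follows from the wording and the model and needs no numerical assumption. If the authors meant subgroup-level HRs, only the wording needs correcting.
- **Declaration rule.** Six to eight interaction tests on the primary outcome are declared significant at unadjusted p ≤ 0.05 without an exploratory label. Under independence, the chance of at least one false declaration is 26% to 34%. That is the upper end of the plausible range, because the modifiers overlap. The count assumes one test per modifier.

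This concerns interpretation and presentation. The primary estimate, its test and the superiority decision do not change.

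**What to change.** Make two changes to Subgroup analyses.

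1. **Plot.** Replace the forest-plot sentence with, for example: *For each subgroup level, the treatment hazard ratio (LAA closure versus open LAA) and its 95% CI, estimated from the interaction model, will be shown in a forest plot with the interaction p-value alongside.*
2. **Rule.** Replace the p ≤ 0.05 declaration with, for example: *All subgroup analyses, including those on the primary outcome, are exploratory. Interaction p-values are reported unadjusted together with the number of tests performed, and no subgroup effect is declared on a p-value alone.* Stating whether pre- and postoperative therapy are tested separately would fix that number.

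The cost is about two sentences and a different figure from the same models. The label does not lower the error rate; it stops a chance result from being reported as an established subgroup effect. The one thing given up is the sponsor's rule for declaring a subgroup effect significant.

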### Missing data

No missing data is anticipated for the primary analyses (time-to-event statistics) of the primary and secondary outcomes. In secondary (sensitivity) analyses, missing data will be handled by multiple imputation with the fully conditional specification method. If patients retract their consent after randomization, follow-up data gathering stops at the retraction date. The follow-up data will be included in the analyses unless the patients request that their data is deleted.

### Additional analysis

#### Long-term follow-up studies

Intended long-term follow-up studies entail a review of patients’ health records for new primary and secondary events after 5 and 10 years, as calculated from the last enrolled patient’s randomization date.

#### Planned substudies

The substudies will be analyzed and published separately from the main study publications and are briefly described.ECG substudy: The aim is to improve the prediction of (1) postoperative AF and (2) postoperative stroke, including TIA, using AI-based ECG and clinical data. A baseline ECG has been obtained for all patients.wavECG substudy: the aim is to identify the presence of an arrhythmogenic substrate using wavECG (Myovista electrocardiogram, HeartSciences, Southlake, Texas, USA) data along with clinical data and biological biomarkers such as blood and tissue samples. A baseline wavECG has been obtained for a subgroup of patients, expected *n* = 200.The imaging substudy: the aim is to evaluate LAA closure efficacy. A subgroup of ten consecutive patients at each site will be examined by transesophageal echocardiography, cardiac CT, or MRI, as applicable at each site. In addition, patients with LAA closure developing ischemic stroke, including TIA, are recommended an examination of their LAA. An estimated 50 patients are included.Holter substudy: the aim is to evaluate the burden of asymptomatic AF recurrence. Patients with new-onset AF after index surgery and sinus rhythm at discharge may be invited for ambulatory continuous cardiac rhythm monitoring approaching the end of follow-up. Patients with an AF episode during follow-up will not be eligible for monitoring. It is estimated that 100 patients will be monitored.

### Harms

The epicardial LAA closure procedures that will be used in this trial are deemed safe and are commercially available. Nonetheless, the following safety outcomes will be systematically recorded and used for annual safety assessments.

**Table Tabe:** 

Item	Time frame
Bleeding (BARC 3a, 3b, 4)^*^	Within 30 days from index surgery
Infection	
Redo cardiac surgery^#^	
Re-hospitalization due to • Pericardial effusion • Pleural effusion • Pericardial infection • Acute decompensated heart failure • Bleeding (BARC 2–4)^*^	30 days from index surgery until the end of follow-up

^*^The Bleeding Academic Research Consortium (BARC) criteria define bleeding events [21]. ^#^Including redo surgery due to device failure or injury caused by device placement

All randomized patients undergoing index surgery will be included in the safety analysis data set. The number and frequencies of the adverse events in each allocation group will be presented in tables alongside descriptive statistics.

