## Analysis

### Outcome definitions

#### Primary outcome

**Table Tabb:** 

Outcome	Definition	Time frame
Stroke and TIA	The occurrence of stroke, including TIA. Both are considered clinical diagnoses constituted by acute focal or global neurological symptoms brought on by thromboembolism or hemorrhage in the brain. The event is defined as a TIA if symptoms last less than 24 h. If patients with a stroke diagnosis receive thrombolytic treatment leading to complete symptom remission, the event is considered a stroke. If patients are diagnosed with amaurosis fugax, the event will be regarded as a TIA. If patients are diagnosed with retinal artery occlusion, the event will be considered a stroke. The stroke subtypes will not be discerned in the primary outcome analyses, i.e., both ischemic and hemorrhagic types are included. The first adjudicated primary outcome is included, while later occurring events are disregarded.	2 years from index surgery

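### The 30-day bleeding row skips BARC 3c and neither bleeding row goes above grade 4, so early 3c bleeds and bleeds graded as fatal are missing from the bleeding counts

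*SAP article*

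**What the plan says.** The Harms section states that "the following safety outcomes will be systematically recorded and used for annual safety assessments". The table that follows has two bleeding items.

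- The early item is "Bleeding (BARC 3a, 3b, 4", with the time frame "Within 30 days from index surgery".
- The later item is "Bleeding (BARC 2–4". It is one of five listed causes of re-hospitalization, from day 30 to the end of follow-up.

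The grades themselves are defined only by a citation in the footnote. For the final report, "The number and frequencies of the adverse events in each allocation group will be presented in tables alongside descriptive statistics".

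Two other parts of the SAP bear on the point. The primary outcome covers "acute focal or global neurological symptoms brought on by thromboembolism or hemorrhage in the brain", and "both ischemic and hemorrhagic types are included". All-cause mortality is listed under Other outcomes and is also a component of the third secondary outcome.

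**The concern.** A bleeding item should not lose a patient because the bleed was of a graver kind. Here grade 3 is split in the early row and its third part is left out, although the grades on either side of it (3b and 4) are counted. The later row takes grade 3 whole. Both rows stop at 4, and the SAP gives no reason for either choice.

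Safety of the added procedure is a stated secondary objective, and the Framework section posits no difference between arms on safety. The comparison consists of counts by arm, so the list of grades decides what is compared. The same list feeds the annual assessment by the Data Safety Monitoring Board, in a trial with no interim analyses.

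**Working it through.** The SAP gives no bleeding rate, expected count or power for bleeding, so there is no figure to reproduce. The check sets the two rows side by side and then looks for where the omitted events would be counted.

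**Step 1. Grades listed in each row (Harms table)**

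| BARC grade | Within 30 days | After 30 days |
|---|---|---|
| 2 | not listed | listed, if re-hospitalized |
| 3a, 3b | listed | listed, if re-hospitalized |
| 3c | not listed | listed, if re-hospitalized |
| 4 | listed | listed, if re-hospitalized |
| above 4 | not listed | not listed |

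This needs no outside source. A 3c bleed on day 10 is not counted; a 3c bleed on day 40 with re-admission is. After day 30, a bleed that kills before re-admission is not counted, whatever its grade.

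**Step 2. What the omitted grades mean (assumption)**

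The SAP does not define the grades. On the usual scale, 3c is intracranial or intraocular bleeding and 5 is fatal bleeding. The early row then omits intracranial bleeds graded 3c, and both rows omit bleeds graded 5.

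**Step 3. Where else the omitted events are counted**

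- A brain hemorrhage with acute symptoms is a primary outcome event from index surgery on. Subtypes are pooled in that analysis, so it sits among the ischemic events that closure is meant to reduce. Subtracting the ischemic stroke outcome from the primary outcome does not isolate it, because that outcome requires a matching lesion on a scan. The remainder would also hold events without such a scan finding.
- A fatal bleed is a death in all-cause mortality and in the mortality-and-stroke composite. Neither is defined by cause.
- A device-related bleed that leads to re-operation can appear under redo cardiac surgery, which the footnote extends to injury from device placement. This is not labelled as bleeding and depends on a re-operation taking place.

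**Step 4. What is on the safety list**

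The list consists of bleeding, infection, redo cardiac surgery and five causes of re-hospitalization. Neither stroke nor death is on it. The board may be shown more, but the SAP does not say so.

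**Step 5. Size**

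The number affected depends on a bleeding risk that the SAP does not give. As a scale only: each 0.1% of patients with an omitted bleed is 1500 × 0.001 = 1.5 patients across both arms. With assumed 30-day risks of 0.2–0.5% for fatal and 0.1–0.3% for intracranial bleeding, this gives 1500 × 0.002 to 0.005 = 3 to 7.5 and 1500 × 0.001 to 0.003 = 1.5 to 4.5. These are illustrations, not estimates.

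**The case against.** The strongest reply has four parts.

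1. **The meaning of 3c and 5 comes from a source that the SAP only cites.** This stands as a limit. Whether an early intracranial or fatal bleed could also be graded 4, and so be counted, cannot be settled from the SAP. Nor does it say that a patient is counted only under the worst grade. The skipped 3c, the stop at 4 and the re-admission condition are visible without the source.

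2. **The events are compared by arm elsewhere.** This also stands. A reader might infer that the worst bleeds disappear from the trial; the SAP does not support that, given its primary outcome and its mortality outcomes. What is lost is their identification as bleeding, and pooled stroke and all-cause death do not restore it.

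3. **Two different ranges are a design choice.** Bleeding soon after open-heart surgery and later re-admission for bleeding are different events, so a lower threshold in the later row (grade 2) is defensible, and the reason may be in the full protocol. Leaving out 3c may also be deliberate, to avoid double counting with stroke. Neither explains a stop at 4 in both rows, and a wish to avoid double counting would need to be stated.

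4. **No bias is shown.** A reader might infer that the rule favors the more dangerous arm. That follows only if the omitted grades occur unequally between arms, and nothing in the SAP shows that they would. Safety is descriptive and unpowered, so no planned test changes.

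**Conclusion.** The point holds as a defect in how bleeding is scored. The 30-day row omits 3c, which the later row includes; neither row reaches a grade above 4; and the later row depends on re-hospitalization. Followed literally, and on the usual meaning of the grades, the bleeding counts for the annual review and the final safety table leave out early 3c bleeds and bleeds graded 5. The trial still captures symptomatic brain hemorrhage and death, but without showing them as bleeding.

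The size is unknown and cannot be derived from the SAP. The primary analysis is unaffected. The change is worth making because the omitted grades are, on that assumption, among the gravest and the remedy is cheap.

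**What to change.** - Define the 30-day row as BARC 3 (a–c), 4 and 5, and the later row as BARC 2–5.
- Count fatal bleeds in the later period whether or not the patient was re-hospitalized.
- Show 3c and 5 as separate lines in each period, so that overlap with the stroke and mortality outcomes is visible.
- Apply the same definitions to the annual safety tables and the final report.

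The cost is mainly wording. Deaths are already recorded and neurological events are already drawn from the charts, but each death would have to be reviewed and attributed to bleeding or not. Some events will then appear under two outcomes, which a table footnote should say.

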### Framework

The hypothesis testing framework is that of a superiority trial. The hypothesis being tested is that LAA closure is superior to leaving the LAA open when concerning the primary outcome. Moreover, that there is no difference between LAA closure and leaving the LAA open when considering safety outcomes. No power calculations have been performed for the safety outcomes.

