### Timing of outcome assessments

The primary and secondary outcomes will be assessed at discharge, 3 months after surgery, and then annually until the end of follow-up.

Safety outcomes will be assessed 30 days after index surgery and, subsequently, at the same time intervals as the abovementioned outcomes.

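### The safety table leaves early readmissions for effusion, heart failure or BARC 2 bleeding, and probably late redo surgery, without an item, and does not match the stated assessment schedule

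*SAP article*

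**What the plan says.** The SAP article's Harms section states that "the following safety outcomes will be systematically recorded and used for annual safety assessments". The table that follows has four items and two time frames.

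- The early frame, "Within 30 days from index surgery", is printed beside bleeding of BARC grades 3a, 3b and 4. The cells beside infection and redo cardiac surgery are blank. A footnote to redo surgery reads: "Including redo surgery due to device failure or injury caused by device placement".
- The late frame, "30 days from index surgery until the end of follow-up", belongs to re-hospitalization. Its five causes are pericardial effusion, pleural effusion, "Pericardial infection", heart failure and bleeding, the last with a wider grade range, "Bleeding (BARC 2–4").

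The section Timing of outcome assessments states: "Safety outcomes will be assessed 30 days after index surgery and, subsequently, at the same time intervals as the abovementioned outcomes". It limits no item to one period.

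The Framework section adds the hypothesis that "there is no difference between LAA closure and leaving the LAA open when considering safety outcomes" and says that safety was not powered. The Harms section plans only counts, frequencies and descriptive statistics by arm.

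**The concern.** Safety of the added closure is one of the secondary objectives, and the Background says that safety in patients without AF and at low stroke risk is still unknown. The table decides which events an analyst counts. If an event type falls between the two frames, it is missing from the arm comparison even when the sites know of it.

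Two gaps stand out. Readmission for pericardial effusion is a listed harm, but only from day 30. Redo surgery is defined to include device failure, and the plan gives no reason why that should stop mattering at day 30. The same items feed the annual safety assessments, so a gap in the table would carry over into that part of what the Data Safety Monitoring Board sees.

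**Working it through.** **The plan's own figure.** There is none for safety. The sample size of 1302 (enlarged to 1500) rests on stroke rates alone, and no safety event rate is given. The check is therefore a comparison of texts.

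**Step 1: place each kind of event in the table.** Entries marked * depend on reading the blank cells as merged with the 30-day frame above them.

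| Event | Before day 30 | After day 30 |
|---|---|---|
| Readmission for pericardial or pleural effusion | no item | counted |
| Readmission for heart failure | no item | counted |
| Readmission for BARC 2 bleeding | no item | counted |
| Readmission for BARC 3a, 3b or 4 bleeding | counted as bleeding | counted |
| Bleeding of those grades without readmission | counted as bleeding | no item |
| Readmission for pericardial infection | counted as infection | counted |
| Other infection | counted | no item* |
| Redo cardiac surgery, including device failure | counted | no item of its own*; visible only if the admission has a listed cause |

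The first three rows do not depend on the blank cells, because the late frame is printed directly against the re-hospitalization item.

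**Step 2: length of the uncovered period.** Analysis methods gives a follow-up of at least two years, about 730 days. The early frame covers 30 / 730 = 4.1% of it. On the merged-cell reading, redo surgery has no item of its own for 100% − 4.1% = 95.9%, about 96%, of minimum follow-up. This is a share of time, not of events. For readmissions the uncovered period is at most the first 30 days.

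**Step 3: compare with the schedule.** Timing of outcome assessments puts all safety outcomes on a 30-day assessment followed by the long-term schedule. Read plainly, redo surgery and infection continue to be assessed after day 30. The table, on the merged-cell reading, stops counting them there. An analyst cannot tell which governs.

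**Step 4: precision, for the minor point on the no-difference hypothesis.** With 1500 / 2 = 750 patients per arm and an assumed common risk p, the 95% half-width for a risk difference is 1.96 × √(2p(1−p)/750):

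- p = 2%: 1.96 × √(0.0392/750) = 1.4 percentage points
- p = 5%: 1.96 × √(0.095/750) = 2.2 percentage points
- p = 10%: 1.96 × √(0.18/750) = 3.0 percentage points

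The three risks are assumptions. The half-widths show general precision only. They would be the same with perfect time frames and do not measure lost events.

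**The case against.** The strongest reply is that the table loses much less than it first seems to. A reader might infer that every harm is counted in only one period, that all early readmissions are lost, and that late redo surgery never enters the comparison. The table does not support any of these. Bleeding appears in both periods, although with different grades and, later, only with an admission. Infection returns later as pericardial infection. Early readmissions for infection or for BARC 3a, 3b or 4 bleeding count under the early items. A late redo may surface through a listed cause of readmission. All of this stands.

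The redo gap also rests on blank cells, which may be an effect of text extraction. That stands as a caveat. The gap for early readmissions does not depend on it.

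It can be said that the schedule section shows safety outcomes being followed throughout, so no hard stop at day 30 was meant. That may be the intention, but then the table should say so. It can also be said that the schedule gives visit dates and the table gives counting periods, so that the 30-day visit serves the early items and later visits serve the late one. On that reading the two sections are compatible, but the gaps in the table remain.

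A reader might further infer that the plan will test safety and claim equivalence from a non-significant result. It does not: it names no safety test, margin or decision rule, and it discloses that safety was not powered. Nor does the document say that the Data Safety Monitoring Board sees only these items. The section on stopping guidance speaks of adverse events generally, and their collection may be set out in the protocol, which is not shown.

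**Conclusion.** The concern holds in a limited form. As printed, readmissions before day 30 for pericardial effusion, pleural effusion, heart failure or BARC 2 bleeding have no item. On the natural reading of the blank cells, redo surgery after day 30 has no item of its own, and infection after day 30 is seen only as readmission for pericardial infection. The table also does not match the plain reading of the assessment schedule, and the two need to be reconciled.

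Following the table as written would give an incomplete comparison for a stated objective. How incomplete cannot be calculated without safety event rates; the 96% is follow-up time and depends on the merged-cell reading. The primary efficacy analysis is not affected. The no-difference wording is a minor matter, because only descriptive tables are planned. The point should be corrected before the safety data are tabulated.

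**What to change.** Reconcile the Harms table with Timing of outcome assessments:

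- Count each safety item from index surgery to the end of follow-up, with readmissions counted from discharge.
- Tabulate each item by arm for 0–30 days and for the period after day 30.
- Use the same BARC grades in both periods.
- Give every item, including infection and redo surgery, an explicit time frame instead of a blank cell.

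As a minor addition, report a risk difference with a 95% confidence interval for each item, and reword the Framework hypothesis on safety as estimation with no claim of equivalence.

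The cost is a change of wording in the SAP and, where needed, in data collection, plus some retrospective chart look-up for patients already past day 30. The document does not say whether the charts already reviewed cover both periods, so the size of that look-up is unknown.

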### Sample size

Based on previous studies, estimated event rates are 1.2% vs. 3.0% per year for patients with and without LAA closure, respectively [8, 9, 11, 16, 18, 19]. A total of 1302 patients need to be included if they are randomized 1:1, followed for 2 years, and a significance level of 0.05 and 90% power is to be achieved. With these numbers, 16 primary events are expected for patients with LAA closure and 39 for patients with an open LAA. The trial will enroll 1500 patients to account for deviations in treatment allocation and death. Please see the trial protocol for more details [20].

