### Analyses of the populations

All outcomes will be analyzed as intention-to-treat (ITT) and per-protocol (PP). In the ITT analyses, the assigned randomization is the basis of the segregation of treatment groups. Only data from patients with LAA status congruent with randomization will be included in the PP analyses.

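### No planned safety table shows harms in everyone who received an LAA closure at index surgery; device harms in open-arm patients closed at that operation are counted under open LAA or, if the per-protocol rule applies, dropped

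*SAP article*

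**What the plan says.** The SAP article defines the safety set in its Harms section: "All randomized patients undergoing index surgery will be included in the safety analysis data set". The same paragraph fixes the grouping: "The number and frequencies of the adverse events in each allocation group will be presented in tables alongside descriptive statistics". One of the listed harms is redo cardiac surgery, and its footnote covers reoperation because the device failed or because placing it caused injury.

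Four other sections bear on this:

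- **Framework** states as a hypothesis that "there is no difference between LAA closure and leaving the LAA open when considering safety outcomes", and adds that "No power calculations have been performed for the safety outcomes".
- **Sample size** expects departures from allocation: "The trial will enroll 1500 patients to account for deviations in treatment allocation and death". It gives no rate for them.
- **Analyses of the populations** says that all outcomes get both an intention-to-treat and a per-protocol (PP) analysis, and defines the latter: "Only data from patients with LAA status congruent with randomization will be included in the PP analyses".
- **Adherence and protocol deviations** reports adherence as a proportion of the intended allocation. It stops follow-up when a closure is done on clinical indication after index surgery, and reports those cases separately.

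No section plans a table of adverse events by the LAA procedure that the patient actually received.

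**The concern.** The last of the Secondary objectives asks about the safety of the closure procedure. Some of the listed harms, device failure and placement injury above all, can occur only in a patient in whom a device was used. If an open-arm patient is given a closure at index surgery and is then reoperated for device injury, the allocation table shows the event under open LAA, a treatment that cannot cause it. A closure-arm patient whose LAA was left untouched adds to the closure denominator without being exposed.

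If closure does cause harm, both kinds of crossover shrink the contrast between the arms. For a superiority question on stroke, that shrinkage is conservative. For a harm question it works the other way, because it moves the comparison toward the absence of difference that Framework hypothesises.

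**Working it through.** **What the plan's own figures give.** The SAP has no figure for the safety comparison. Its sample size reproduces: two-year risks of 2.4% and 6.0%, two-sided 5% level, 90% power and a pooled-variance two-proportion formula give 651 per arm, or 1302. Expected events are 651 × 0.024 = 15.6 and 651 × 0.06 = 39.1. The step from 1302 to 1500 (198 patients) covers allocation deviations and death together, so no crossover rate can be read from it. Crossover rates and harm rates below are therefore assumptions.

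**Dilution.** Let r be the harm risk with the LAA untouched and d the excess from closure. Let c_open be the share of open-arm patients closed at index surgery, and c_closure the share of closure-arm patients left open. Suppose harm follows the procedure received and crossover is unrelated to risk. Then:

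- closure-arm risk = r + d(1 − c_closure)
- open-arm risk = r + d·c_open
- observed difference = d(1 − c_open − c_closure)

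| Assumed rate | Open arm only: 1 − c | Both arms: 1 − 2c |
|---|---|---|
| 2% | 98% | 96% |
| 5% | 95% | 90% |
| 10% | 90% | 80% |

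**Illustration for a fairly common event.** Assume r = 5%, d = 2 points and 750 per arm. Without crossover the risk ratio is 7.0/5.0 = 1.40, and a two-sided 5% test has 37% power.

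| c_open / c_closure | Closure arm | Open arm | Risk ratio | Power |
|---|---|---|---|---|
| 5% / 0 | 7.0% | 5.1% | 1.37 | 34% |
| 10% / 0 | 7.0% | 5.2% | 1.35 | 31% |
| 5% / 5% | 6.9% | 5.1% | 1.35 | 31% |
| 10% / 10% | 6.8% | 5.2% | 1.31 | 26% |

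Most of the weakness is already there without crossover.

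**Device-specific events.** Here r = 0, so every event belongs to a patient who had a closure. The expected share listed under open LAA is c_open / (c_open + 1 − c_closure). That is 0.05/1.05 = 4.8% at 5% open-arm crossover only, 0.05/1.00 = 5% at 5% in both arms, and 0.10/1.00 = 10% at 10% in both arms. The share is small, but when such events are few, one or two cases under the wrong arm can be much of what there is to see.

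**What the per-protocol rule would do.** Under the same assumptions it removes crossovers from both arms and brings the risk ratio back to 1.40. It does not move the crossover patient's device harm to closure; it deletes it. If a failed attempt leaves the LAA open, a closure-arm patient in whom closure was tried would be deleted too, along with any injury from the attempt.

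**Closures after index surgery.** Follow-up is halted at the moment of closure, so later harms are not charged to the open arm.

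**The case against.** The strongest reply is that the plan does not rely on allocation alone. The Harms items are called safety outcomes in several sections, and Analyses of the populations says all outcomes are also analysed per protocol. Read literally, a second safety analysis without crossovers is planned, and it removes the dilution calculated above. This stands, so a reader who infers that safety is analysed by allocation only goes too far. What remains is that the Harms section does not mention the rule, that Analysis methods and Sensitivity analyses present per-protocol work as a check on the primary analyses, and that on either reading no table shows all patients who had a closure.

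A second reply is that allocation grouping preserves randomization, while index-surgery crossover may well depend on operative findings, so a comparison by procedure received could be biased in either direction. This also stands. It argues against making the as-received table the main one, but not against showing it beside the other.

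Third, the Harms section plans counts and descriptive statistics only. There is no margin, test or decision rule for safety that dilution could overturn. This is correct and limits what is at stake.

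Finally, a reader might infer that later closures are charged to the open arm, or that the Data Safety Monitoring Board sees events by allocation only. The documents do not support either. Later closures are halted and reported separately, and the grouping used in the annual assessments is not stated.

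**Conclusion.** The point holds as a reporting gap with a cheap remedy. The safety tables are by allocation, and harms in open-arm patients closed at index surgery appear under open LAA or, if the per-protocol rule applies, not at all. Under assumed crossover of 2% to 10%, allocation tables keep 98% to 90% of a true risk difference when only the open arm crosses over, and 96% to 80% when both arms do. These figures assume that harm follows the procedure received and that crossover is unrelated to risk. The effect is modest for common events and can matter for rare device-specific ones.

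The documents do not support calling the safety comparison materially biased: they give neither a crossover rate nor a harm rate.

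**What to change.** In the Harms section:

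1. Keep the table by allocation group.
2. Add a second table for all operated patients by procedure actually received at index surgery (closure attempted or performed against LAA untouched), with device-related events listed under closure. Label it as a non-randomized comparison.
3. State whether the per-protocol rule in Analyses of the populations applies to safety outcomes.
4. Make the as-received table available for the annual safety assessments.

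The cost is one extra table. Adherence reporting already requires the procedure performed to be recorded, and the adverse events are collected anyway. The downside is that the added comparison is not protected by randomization, which is why the allocation table stays.
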